## **Supplementary 2 Statistical Plan**

### **TITLE: A RANDOMIZED CONTROLLED TRIAL COMPARING GRADUAL AND IMMEDIATE BRACE WEANING FOR CLINICAL MANAGEMENT OF ADOLESCENT IDIOPATHIC SCOLIOSIS PATIENTS**

#### **DATA PROCESSING AND ANALYSIS**

##### **1. SAMPLE SIZE CALCULATION**

The sample size of this clinical trial will be determined based on an independent sample *t*-test to detect a difference between the two groups (immediate and gradual bracing weaning) for the changes in Cobb angle. According to a previous study [1], the average increase in Cobb angle at 1 year after brace weaning was 3.5 degrees. Curve progression is observed in 43.5% of patients. At 2 years, the curve progression rate was 46.5% with an average increase of major curve Cobb angle of 5.1 degrees. Based on this result, we consider a difference of 2 degrees between the changes in Cobb angle as clinically relevant, with an equivalence margin of 0.4. Assuming a standard deviation of 6 degrees for the Cobb angle change, a sample of 128 per group is required to detect the difference of the statistical test with 80% power at a 0.05 level of significance. Accounting for 20% overall attrition rate at 1 year follow-up, we will recruit 308 AIS patients (154 in each group) for this prospective study.

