## **2. SECONDARY ANALYSES**

The secondary efficacy analyses will be based on one-way analysis of covariance (ANCOVA) with post-hoc Bonferroni correction for intergroup comparisons. The ANCOVA model is used to analyze the effect of brace weaning protocols on the outcomes of changes of major curve Cobb angles and truncal balance as well as HRQoL measures, whilst adjusting for baseline covariates. Baseline covariates will be identified through testing the relationships of baseline parameters including socio-demographics, body size, maturity parameters, and other baseline radiographic measurements with the study outcomes using correlation tests.

The comparison between groups will be carried out using the adjusted mean

difference between the study groups at all post-weaning time points. The estimated difference between the two weaning protocols will be displayed along with the associated 95% confidence interval and p-value. The analysis will be carried out according to intention-to-treat (ITT) and PP principle.

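### Neither 128 nor 154 per group follows from the stated inputs: after the planned 20% attrition, two-sided power for 2 degrees is about 74%, not 80%

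*Supplement*

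**What the plan says.** All the inputs are in Supplementary 2 (Statistical Plan), section 1, Sample Size Calculation.

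- **Test:** "The sample size of this clinical trial will be determined based on an independent sample" t-test on the change in Cobb angle, "to detect a difference between the two groups".
- **Effect:** "we consider a difference of 2 degrees between the changes in Cobb angle as clinically relevant", followed by "with an equivalence margin of 0.4", with no unit or role given for the margin.
- **SD and base sample size:** "Assuming a standard deviation of 6 degrees for the Cobb angle change, a sample of 128 per group is required to detect the difference".
- **Error rates:** "with 80% power at a 0.05 level of significance". Sidedness is not stated.
- **Attrition:** "Accounting for 20% overall attrition rate at 1 year follow-up, we will recruit 308 AIS patients (154 in each group) for this prospective study".

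Two later provisions matter. The opening paragraph of the Statistical Analysis section rules out imputation. Section 1, Primary Analysis, makes the primary test an unadjusted two-sample t-test and limits the intention-to-treat set to patients whose outcome was observed.

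**The concern.** The section gives every input to a standard calculation except sidedness, so 128 should be reproducible, and it is not. The step from 128 to 154 looks like a separate slip: multiplying by 1.2 does not undo a 20% loss. Both errors make the trial smaller than its two-sided power claim requires, and nothing else in the primary analysis absorbs the loss, since patients without an outcome drop out of the test.

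What is at stake is how a null result is read. Readers told that the trial had 80% power for 2 degrees will take a non-significant result as stronger evidence against such a difference than the design supports.

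**Working it through.** **Inputs** (SAP section 1): difference δ = 2, SD σ = 6, so d = 2/6 = 0.333; power 0.80; α = 0.05; 1:1 allocation; attrition 20%. Sidedness is not given, so both cases are shown.

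**Step 1. Can 128 be reproduced?** Normal approximation: n per group = 2(z_α + z_β)²σ²/δ².

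- Two-sided: 2 × (1.960 + 0.8416)² × 36/4 = 141.3, so 142. The exact noncentral-t solution is 142.2, so 143.
- One-sided: 2 × (1.645 + 0.8416)² × 36/4 = 111.3, so 112. The noncentral-t solution is 111.97, also 112.

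Neither gives 128. Reading the 0.4 as part of the hypothesis does not help. At 80% power:

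| Reading | α = 0.05 per side | α = 0.025 per side |
|---|---|---|
| Equivalence (two one-sided tests), margin 2 | 155 | 190 |
| Equivalence, margin 2.4 (0.4 SD, or 2 + 0.4) | 108 | 132 |
| Equivalence, margin 0.4 degrees | 3,854 | 4,729 |
| Non-inferiority, margin 2.4 | 78 | 99 |
| Non-inferiority, margin 0.4 degrees | 2,783 | 3,532 |

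Figures near 128 need inputs that the SAP does not state. An SD of 5.69 gives 128 two-sided, and a one-sided test at 85% power gives 130.

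**Step 2. Attrition.** To keep n evaluable after a fraction a is lost, recruit n / (1 − a).

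- Plan's figure reproduced: 128 × 1.2 = 153.6, so 154.
- Required: 128 / 0.8 = 160 per group, 320 in total.
- Left after 20% loss: 154 × 0.8 = 123.2, about 123, below the plan's own 128.
- Loss that 154 can absorb while keeping 128: 1 − 128/154 = 16.9%.

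This step does not depend on sidedness.

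**Step 3. Power** (noncentral t, d = 0.333):

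| Evaluable per group | Two-sided 0.05 | One-sided 0.05 |
|---|---|---|
| 154 (no loss) | 83.0% | 89.9% |
| 128 | 75.7% | 84.5% |
| 123 (20% loss) | 74.0% | 83.2% |

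As a hand check of the two-sided 123 row: √(123/2) × 0.333 − 1.960 = 0.654, and Φ(0.654) = 0.744 by the normal approximation.

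Two-sided, the difference detectable with 80% power is 2.11 degrees at 128 per group and 2.15 degrees at 123.

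**Step 4. A consistent size.** Two-sided with 20% loss: 143 / 0.8 = 178.75, so 179 per group and 358 in total.

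**Step 5. The 24-month comparison.** The SAP gives no attrition figure for 24 months. If 25% to 30% were lost (my assumption), 154 × 0.75 ≈ 116 and 154 × 0.70 ≈ 108 would remain per group, with two-sided power of 71.5% and 68.4%.

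**The case against.** The strongest reply is that no passage states sidedness, and the primary hypothesis (final protocol, section 2a) is directional: gradual weaning should maintain the curve better. Under a one-sided 0.05 test, 128 exceeds the 112 needed and power after 20% loss is 83.2%, so the 80% claim would be met. That is a fair caveat: the statements that 128 is too few and that power is about 74% rest on a two-sided test. But an unqualified 0.05 test for a difference is two-sided by ordinary convention, and the secondary analysis section says the group difference "will be displayed along with the associated 95% confidence interval and p-value", which fits a two-sided 0.05 level. A one-sided reading would also leave 128 unexplained and 154 short of 160.

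A second reply is that the effect is modest. The shortfall is about 6 percentage points, the SD is itself an assumption, full retention of 154 would give 83%, and no estimate or type I error rate is affected. All of this is true. It limits the consequences but does not make the sentence correct, because the plan claims 80% under its own 20% attrition.

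The 24-month figures carry little weight: the final protocol (section 3c) puts the primary end point at 1 year and treats the 2-year visit as additional information.

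**Conclusion.** The concern holds. The base figure of 128 follows from the stated inputs under neither sidedness, and 154 per group does not protect 128 against 20% attrition. The second error needs no assumption at all. Taking the test as two-sided, with SD 6 and 20% loss, power for 2 degrees is 74.0% and the type II error is 26% instead of 20%. If the authors did intend a one-sided 0.05 test, power would be about 83%, and the text would still need correcting because its numbers would not follow. This is a moderate error in a central design statement. It does not bias the analysis.

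**What to change.** Correct section 1 of the SAP and leave enrolment as it is:

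1. State the sidedness of the primary test. The wording implies two-sided; if one-sided was intended, say so and give the matching figures (112 per group required; 83% power at 123).
2. Replace the 128 and 154 derivation. For a two-sided test, for example:

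> With 308 patients (154 per group) and 20% attrition at 1 year, about 123 per group will be evaluable. This gives 74% power (two-sided α = 0.05) for a 2-degree difference in Cobb angle change with SD 6, or 80% power for a difference of 2.15 degrees.

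3. Define the 0.4 equivalence margin (unit, hypothesis, test) or delete it. Otherwise the hypothesis behind the calculation stays unclear.

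The cost is SAP wording and a less favourable stated power. Meeting 80% for 2 degrees under the stated assumptions would instead take 358 patients, 50 more than planned.

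Making a baseline-adjusted analysis primary could recover some power without extra patients, since the SAP already plans ANCOVA as secondary. The gain depends on a correlation the documents do not give. At 123 per group, an assumed covariate–outcome correlation of 0.2 gives 75.7% power and 0.4 gives 81.1%.

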##### **2. STUDY OUTCOMES**

Primary outcome was the change in major curve Cobb angle from baseline to 6-month, 12-month, and 24-month follow-up. Curve progression was examined as  $>5^\circ$  increase of major Cobb angle between follow-up time points and baseline. Secondary outcomes were the change in truncal balance in truncal shift and listing (C7-central sacral vertebral line deviation) from baseline to 6-month, 12-month and 24-month follow-up.

Secondary outcomes also included the refined Scoliosis Research Society 22-item (SRS-22r) questionnaire total score, the EuroQol-5-dimension (EQ-5D) utility score and EuroQol-visual analogue scale (EQ-VAS) at all post-weaning time points.

All study outcome measures were studied at baseline (the time of weaning), post-weaning 6, 12 and 24 months.

Body weight, standing and sitting body height, arm span, and HRQoL measures were measured, and curve type (i.e. thoracic, thoracolumbar/ lumbar) and coronal Cobb angle were assessed from whole spine standing posteroanterior and lateral radiographs taken simultaneously at each visit as per clinical routine. Skeletal maturity was routinely determined at the time of weaning using Risser staging, distal radius and ulna (DRU) classification and Sanders staging. In addition to Cobb angle and truncanl balance, other radiological parameters including T1 tilt, shoulder height, sagittal vertical axis (SVA), thoracic kyphosis (T5-12) and lumbar lordosis (L1-S1) were measured by two assessors independently. An intra-class correlation coefficient (ICC) with 95% confidence interval will be used to estimate the inter-assessor reliability.

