### **c. Study Duration**

All subjects will be followed-up longitudinally the primary end point at 1 year after brace weaning has been issued. A final assessment time point at 24 months is added to assess the long term efficacy [25] of weaning protocol in the maintenance of curve magnitude and truncanal balance. Therefore, this includes three clinic visits with one at 6 months to complete the gradual brace weaning protocol, another at 1 year and a final visit at 2 years to observe for any delayed changes to the overall curvature and balance, including loss of truncanal balance and Cobb angle deterioration. This follow-up duration is based on previous work suggesting that the highest risk of post-brace weaning curve progression occurs within 6 months of stopping brace wear.[24] A 1-year collection of data is adequate for seeing differences between the two groups. This does not deviate significantly from our usual care as all AIS subjects in our clinic are followed-up at 6-monthly intervals. The 2 year visit will offer additional information about the effects of brace weaning protocols in the long term.

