### **Study Outcomes**

#### **a. Primary outcome**

- Change in Cobb angle from baseline to 6 months, 1 year and 2 years follow-up.

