### 1. PRIMARY ANALYSIS

The primary analysis will be evaluated by two independent sample *t*-test to determine the significance of the differences in change of Cobb angle and truncanl balance

between the two groups. The analysis will primarily be carried out according to intention-to-treat (ITT) and subordinately based on per-protocol (PP) principle. The ITT analysis will include any randomized patients with non-missing efficacy measures. The PP analysis will include all randomized patients in ITT who fulfil the criteria of PP population.

The PP population is defined as a subset of the ITT population. Patients will be included in the PP population if they have:

- no late report violations of entry criteria,
- no incorrect treatment group assigned,
- no major protocol deviation(s) that is/are clinically significant to efficacy outcome,
- no treatment during follow-up after weaning, and
- with sufficient treatment compliance.

Sufficient treatment compliance is defined as gradual brace weaning patients having completed at least 8 hours/night of brace-wear for >80% of the 6-month gradual weaning period. Brace-wear compliance (hours/day) for the 6-month gradual weaning period will be recorded by thermal sensor.

Both ITT and PP results will be reported for primary analyse.

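### Protocol and SAP disagree on which test is primary (Cobb change at 1 year, or at three visits with truncal balance added), and no rule allocates the 5% error

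*Supplement*

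**What the plan says.** **One primary time point.** The final protocol's primary aim (section 2a) and its hypothesis concern Cobb angle maintenance one year after weaning. Section 3c (Study Duration) agrees: "All subjects will be followed-up longitudinally the primary end point at 1 year after brace weaning has been issued". It describes the 24-month visit as an addition for long-term information.

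**Three primary time points.** The primary outcome in protocol section 6 reads "Change in Cobb angle from baseline to 6 months, 1 year and 2 years follow-up". SAP section 2 (Study Outcomes) follows it: "Primary outcome was the change in major curve Cobb angle from baseline to 6-month, 12-month, and 24-month follow-up".

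**A secondary outcome in the primary analysis.** SAP, Primary Analysis, uses two-sample *t*-tests "to determine the significance of the differences in change of Cobb angle and truncanl balance". Protocol section 6 and SAP section 2 both list truncal balance as secondary. The SAP measures it by two variables, truncal shift and listing.

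**Error control.** The only significance level stands in the sample size section, which plans one *t*-test on Cobb change "with 80% power at a 0.05 level of significance". The only multiplicity correction is in SAP, Secondary Analyses: "The secondary efficacy analyses will be based on one-way analysis of covariance (ANCOVA) with post-hoc Bonferroni correction for intergroup comparisons". The trial has two arms.

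**The concern.** Three readings of the primary result are open: Cobb change at 12 months; Cobb change at any or all of three visits; or Cobb change and truncal balance together. The SAP, which governs the analysis, never singles out 12 months as the test that decides the trial, so the choice could be made after the results are known.

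The visits are not interchangeable. Under protocol section 3b the gradual arm wears the brace at night for six months, so at the 6-month visit it has only just stopped, while the immediate arm has been without a brace for the whole period. Section 3c places the highest risk of progression within six months of stopping. A difference at 6 months could therefore reflect when the brace came off and not the one-year maintenance that the primary aim asks about. The outcome lists would still allow it to be reported as a primary result.

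At stake are the 5% error rate on which the sample size rests and the clarity of the trial's main claim.

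**Working it through.** **1. The plan's own figure.** Inputs from SAP section 1: difference 2 degrees ("we consider a difference of 2 degrees between the changes in Cobb angle as clinically relevant"), SD 6 degrees ("Assuming a standard deviation of 6 degrees for the Cobb angle change"), 80% power, 0.05. Sidedness is not stated; two-sided is assumed.

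n per group = 2 × SD² × (z₀.₉₇₅ + z₀.₈₀)² / difference² = 2 × 36 × (1.960 + 0.842)² / 4 = 141.3, so 142. The exact *t* calculation gives 143.

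The SAP states 128, which I could not reproduce. That is a separate matter. What counts here is that the calculation is for one test at 0.05, with attrition allowed for at 1 year. It has no room for several primary tests.

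**2. Number of tests under each reading.**
- Primary aim and Study Duration: 1 (Cobb, 12 months).
- Outcome lists: 3 (Cobb at 6, 12 and 24 months).
- SAP primary analysis combined with the SAP outcome list: up to 3 measures × 3 visits = 9.

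**3. Chance of at least one false positive**, if each test is at two-sided 0.05 and any one counts as success. Neither condition is written in the documents.

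Independent tests: 1 − 0.95³ = 14.3%; 1 − 0.95⁹ = 37.0%.

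Correlated tests were simulated as multivariate normal z-statistics with the criterion |z| > 1.96. The documents give no correlations, so all are assumed. For nine tests, the correlation matrix is the product of a visit correlation and a between-measure correlation.

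| Visit correlation | Cobb, 3 visits | 9 tests, between-measure correlation 0 | 9 tests, between-measure correlation 0.5 |
|---|---|---|---|
| 0 | 14.3% | 37.0% | 33% |
| 0.5 | 12.5% | 33% | 29% |
| 0.7 | 10.9% | 29% | 26% |
| 0.8 | 9.8% | 27% | 23% |
| 0.9 | 8.4% | 23% | 20% |

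**4. What the named correction does.** Two arms give one between-group comparison, so Bonferroni uses 0.05 / 1 = 0.05. It is attached to the secondary ANCOVA, so it does not touch the primary *t*-tests.

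**5. Cost of the two coherent designs.**
- One primary test at 12 months: error 5%, no correction needed.
- Three primary visits with Bonferroni: 0.05 / 3 = 0.0167 per test, z = 2.394. Then n = 2 × 36 × (2.394 + 0.842)² / 4 = 188.4, so 189 per group for 80% power at each visit.
- Power with 128 per group: standard error = 6 × √(2/128) = 0.75, and 2 / 0.75 = 2.667. At 0.0167, Φ(2.667 − 2.394) = 61%. At 0.05, Φ(2.667 − 1.960) = 76%.

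**The case against.** The strongest reply is that the final protocol does name a primary time point. Its aim, its hypothesis, its Study Duration section and the attrition allowance in the sample size all point to 1 year, and 24 months is plainly an addition. On that reading the primary claim is one test at 5%, ITT is ranked above per-protocol, and nothing is inflated.

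This stands in part. A reader might infer that the plan tests nine primary hypotheses, each at 0.05, and so has a false-positive rate well above 5%. The documents do not support that. The 0.05 level appears once, for the sample size. No text says that any one significant result makes the trial positive. The SAP's primary analysis names no visits and does not split truncal balance; the count of nine comes from combining it with the outcome list, against the explicit secondary status of truncal balance. The Bonferroni concerns the secondary ANCOVA, and the SAP does not define its family, so a factor of one is the natural reading and not a stated one.

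What the reply does not remove is the conflict. The outcome lists of both documents contradict the 1-year end point, and the SAP's primary analysis does not restore it.

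**Conclusion.** The point holds as a conflict over the primary test, with no rule to resolve it; it is not a demonstrated inflation of the error rate. Confidence in the conflict is high, because it rests on the text alone.

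The size is conditional. If any visit counted as success at 0.05, the false-positive rate would be about 8% to 14% for Cobb angle alone (visit correlation 0.9 to 0). The range of about 20% to 37% is an upper case: it also needs truncal shift and listing at all three visits to count (visit correlation 0.9 to 0, between-measure correlation 0.5 to 0). If the 12-month test is fixed in advance as the only primary test, the rate is 5%. It should be settled before analysis, since it decides which result the trial reports as its answer.

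**What to change.** **Primary test.** In protocol section 6 (primary outcome), SAP section 2 (Study Outcomes) and SAP, Primary Analysis, state that the single primary test is the between-group difference in change in major-curve Cobb angle from baseline to 12 months, ITT, two-sided 0.05. Move Cobb change at 6 and 24 months and all truncal-balance tests to secondary. This matches the primary aim and the single-test sample size.

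**Secondary tests.** In SAP, Secondary Analyses, drop the Bonferroni between groups and label the secondary tests as supportive, without error control. If a formal secondary claim is wanted, first list every outcome with its time point, including 6- and 24-month Cobb change, truncal shift, listing, SRS-22r, EQ-5D and EQ-VAS. Then apply a correction such as Holm to that list. The choice between the two is the investigators' to make, but it must be made in advance.

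**Cost.** Wording only, with no added patients. The downside is that a 6- or 24-month result can no longer be reported as the primary result. Keeping three primary visits under Bonferroni would instead need 189 per group, or leave 61% power per visit at 128.

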## STATISTICAL ANALYSIS

All statistical analyses will be carried out using SPSS Statistics v. 28.0 (Armonk, NY, IBM Corp) and sample size calculation will be performed using G\*Power 3.1.9.7. For descriptive statistics, means and standard deviations or medians and interquartile ranges will be presented for continuous variables, frequencies and percentages will be presented for categorical/ discrete variables. No imputation will be performed for missing data.

### 1. PRIMARY ANALYSIS

The primary analysis will be evaluated by two independent sample *t*-test to determine the significance of the differences in change of Cobb angle and truncanl balance

between the two groups. The analysis will primarily be carried out according to intention-to-treat (ITT) and subordinately based on per-protocol (PP) principle. The ITT analysis will include any randomized patients with non-missing efficacy measures. The PP analysis will include all randomized patients in ITT who fulfil the criteria of PP population.

The PP population is defined as a subset of the ITT population. Patients will be included in the PP population if they have:

- no late report violations of entry criteria,
- no incorrect treatment group assigned,
- no major protocol deviation(s) that is/are clinically significant to efficacy outcome,
- no treatment during follow-up after weaning, and
- with sufficient treatment compliance.

Sufficient treatment compliance is defined as gradual brace weaning patients having completed at least 8 hours/night of brace-wear for >80% of the 6-month gradual weaning period. Brace-wear compliance (hours/day) for the 6-month gradual weaning period will be recorded by thermal sensor.

Both ITT and PP results will be reported for primary analyse.

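### The primary ITT analysis is an available-case t-test at each visit, with no model or sensitivity analysis for the 20% loss planned by 1 year

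*Supplement*

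**What the plan says.** The relevant statements are in the Statistical Plan (SAP) and the final protocol.

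- Analysis set (SAP, 1. Primary Analysis): "The ITT analysis will include any randomized patients with non-missing efficacy measures". The per-protocol set is a further subset of this.
- Missing data (SAP, Statistical Analysis): "No imputation will be performed for missing data".
- Primary test (SAP, 1. Primary Analysis): a two-sample t-test on "differences in change of Cobb angle and truncanl balance".
- Secondary analysis (SAP, 2. Secondary Analyses): "The secondary efficacy analyses will be based on one-way analysis of covariance (ANCOVA) with post-hoc Bonferroni correction for intergroup comparisons", on the same two sets and adjusted for baseline covariates.
- Planned loss (SAP, 1. Sample Size Calculation): "Accounting for 20% overall attrition rate at 1 year follow-up, we will recruit 308 AIS patients". No figure is given for 24 months.

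The final protocol (3c, Study Duration) puts the primary end point at 1 year. Outcomes are scheduled at baseline, 6, 12 and 24 months (SAP, 2. Study Outcomes), with radiographs at every clinic visit (final protocol, section 6). The SAP contains no repeated-measures model, no stated assumption about why data are missing, no missing-data sensitivity analysis and no comparison of patients lost with patients retained.

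**The concern.** Membership of a set called ITT depends here on a post-randomisation event, namely having the outcome measured. The comparison is then free of bias only if loss is unrelated to outcome within each arm, or is related to it in the same way in both.

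Neither condition is assured. The trial is open-label, and the arms carry different burdens: one continues night bracing for six months with sensor monitoring, and the other stops at once. The trial's own hypothesis is that the curves behave differently by arm. Progression seen on the 6-month film could therefore influence who returns at 12 months, and differently by arm.

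The difference that the SAP calls clinically relevant is 2 degrees, so a bias of some tenths of a degree is not negligible. For a patient lost after the 6-month visit, the information that would correct such bias is already on file, but the 12- and 24-month analyses ignore it.

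**Working it through.** **Step 1. Size of the analysis set.** Inputs from the SAP sample size section: 154 randomised per arm (308 in all) and 20% loss at 1 year.

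- The plan's inflation step reproduces as 128 × 1.20 = 153.6, rounded to 154.
- Expected at 12 months: 154 × 0.80 = 123 per arm; 308 × 0.80 = 246 in all. Left out: 308 − 246 = 62.
- The plan's 128 per group does not itself reproduce: a two-sided t-test with difference 2, SD 6, 80% power and alpha 0.05 needs 143. That is a separate matter. This point uses only the 20% and the 308.

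**Step 2. If loss is completely at random.** There is no bias. Two-sided power for 2 degrees with SD 6 is 74.0% with 123 per arm, against 83.0% with all 154. The standard error of the difference with 123 per arm is 6 × √(2/123) = 0.77 degrees. Simulated power (154 per arm, 4,000 runs per scenario) when the 6-month value is also used, for an assumed correlation between 6- and 12-month change of 0.5, 0.7 and 0.9:

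- all loss after month 6: about 76%, 79% and 82%;
- half of the loss before month 6: about 75%, 77% and 78%;
- available cases only: about 73% to 75%.

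**Step 3. If loss depends on 6-month change in one arm only.** The difference is immediate minus gradual, with a true value of 2 degrees and SD 6. Assumptions not in the documents: 20% loss in each arm, all after month 6; logistic dropout in one arm with log-odds 0.5 to 1.0 per SD of 6-month change; random loss in the other arm. The bias is

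correlation × 6 × (shift in the mean standardised 6-month change among those who stay).

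At correlation 0.7 and log-odds 1.0 in the immediate arm the large-sample estimate is 1.26, so the shift is (2 − 1.26)/(0.7 × 6) = 0.18 SD. At log-odds 0.5 the estimate is 1.59 and the shift is (2 − 1.59)/(0.7 × 6) = 0.10 SD. Over the range of correlations, for log-odds 0.5 to 1.0:

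| Correlation | Worse-doing patients leave the immediate arm | Better-doing patients leave the immediate arm |
|---|---|---|
| 0.3 | 1.8 to 1.7 | 2.2 to 2.3 |
| 0.5 | 1.7 to 1.5 | 2.3 to 2.5 |
| 0.7 | 1.6 to 1.3 | 2.4 to 2.7 |
| 0.9 | 1.5 to 1.1 | 2.5 to 2.9 |

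If better-doing patients leave the gradual arm instead, the estimates are those of the middle column.

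**Step 4. Variations.**

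- Same mechanism in both arms (log-odds 1.0 in each): estimate about 2.0, so no bias.
- Half of the loss random and before month 6, correlation 0.7, worse-doing patients leaving the immediate arm: 1.8 to 1.6. Over the range, the bias is about 40% to 45% smaller.
- A different rule (immediate arm loses 40% of those who progress more than 5 degrees by month 6 and 13% of the rest; gradual arm a flat 20%): 1.66, 1.51 and 1.39 at correlations 0.5, 0.7 and 0.9. With no true difference, the type I error is about 7%, 9% and 10%.
- An estimate that also uses the 6-month value returned about 2.0 in every one of these scenarios, with type I error near 5%. All of them were built so that loss depends only on observed data.

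**The case against.** Several stronger readings are tempting, and the documents do not support them.

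- A reader might call this a completer analysis. It is available-case by visit: a patient lost after month 6 still counts in the 6-month comparison, which the plan also lists under the primary outcome.
- A reader might infer that every patient lost has an unused film. Those lost before month 6 have only the baseline film, and the SAP does not split the 20% by time.
- A reader might infer that the bias dilutes the effect. As the table shows, its sign depends on who leaves which arm. Dislike of night wear need not be related to Cobb change at all.
- Forgoing imputation is not a fault in itself, because a likelihood model needs none. Nor is the set concealed: the SAP states who is in it, and only the label is loose.

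It can also fairly be said that visits follow usual 6-monthly care, which makes strongly selective loss less likely. The documents give no evidence of arm-dependent loss. At correlation 0.7 the one-arm biases of 0.4 to 0.7 degrees are below one standard error (0.77). The baseline-adjusted ANCOVA deals with loss driven by the covariates in it. A mixed model is only as good as its assumptions: at 6 months one arm is just finishing night bracing and the other has been brace-free throughout, so the relation between 6- and 12-month change may differ by arm.

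These points limit what can be said about size and certainty. They leave the gap in place: nothing planned addresses loss that depends on 6-month change, and no sensitivity analysis would reveal it. A bias below one standard error still shifts the estimate and, under the assumed rule in the working, raises the type I error.

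**Conclusion.** The point holds as a gap in the analysis plan that should be closed. The 12-month comparison is expected to omit about 62 of 308 randomised patients, uses none of their 6-month data, and has no stated missing-data assumption or sensitivity analysis behind it.

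That much is certain from the text. The size of any bias is not. The figures of 1.1 to 1.8 degrees, or 2.2 to 2.9 with the selection reversed, for a true 2 degrees rest on the assumed one-arm dropout mechanism, on all loss falling after month 6 and on a correlation that the documents do not give. The bias shrinks if part of the loss is early and random, and vanishes if the mechanism is the same in both arms. If loss is random, only precision is lost.

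**What to change.** - Define ITT as all randomised patients, analysed as randomised.
- Analyse Cobb change at 6, 12 and 24 months with a likelihood-based mixed model for repeated measures: arm, visit, arm × visit, baseline Cobb × visit, and unstructured covariance (arm-specific if the data support it). Name the 12-month arm contrast as the primary test. SPSS, already named in the SAP, fits this with MIXED.
- Keep the t-test as a sensitivity analysis and label it available-case.
- Add one delta-adjusted analysis, shifting the missing 12-month values by arm, for loss that depends on unobserved outcomes.
- Report the numbers lost by arm, before and after the 6-month visit.

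The cost is SAP wording and a little more analysis, with no new data. The downside is a model-based primary analysis in place of a simple t-test. Patients lost before 6 months have only baseline data to offer, so the model recovers little for them and the delta-adjusted analysis has to carry that uncertainty.
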